## Abstract

**Background:**

In this paper we outline the protocol for an implementation-effectiveness trial of *ecofit*, a multi-component mHealth intervention aimed at increasing participation in resistance and aerobic physical activity using the outdoor built environment (i.e., outdoor gyms) and social support. We have previously demonstrated the efficacy and effectiveness of the *ecofit* program in insufficiently active people with (or at risk of) type 2 diabetes and community-dwelling adults, respectively. The objective of this trial is to compare the effects of two implementation support models (i.e., ‘Low’ versus ‘Moderate’) on the reach (primary outcome), uptake, dose received, impact and fidelity of the *ecofit* program.

**Research design and methods:**

This hybrid type III implementation-effectiveness study will be evaluated using a two-arm randomized controlled trial, including 16 outdoor gym locations in two large regional municipalities in New South Wales, Australia. Outdoor gym locations will be pair-matched, based on an established socio-economic status consensus-based index (high versus low), and randomized to the ‘Low’ (i.e., *ecofit* app only) or ‘Moderate’ (i.e., *ecofit* app, face-to-face workout sessions and QR codes) implementation support group. The primary outcome of ‘reach’ will be measured using a modified version of the ‘System for Observing Play and Recreation in Communities’, capturing outdoor gym use amongst community members.

**Conclusion:**

This implementation-effectiveness trial will evaluate the effects of different levels of implementation support on participation in resistance-focused physical activity using mHealth and outdoor gyms across the broader community. This may guide widespread dissemination for councils (municipalities) nation-wide wanting to promote outdoor gym usage.

**Trial registry:**

This trial was preregistered with the Australian and New Zealand Clinical Trial Registry (ACTRN12624000261516).

## Introduction

1

Physical inactivity accounts for 9 % of premature mortality (5.3 million deaths) worldwide and is one of the leading risk factors for non-communicable diseases [1]. In Australia, physical inactivity accounts for 10–20 % of the national disease burden for several major non-communicable diseases (e.g., diabetes, different cancers, dementia, coronary heart disease and stroke) and is responsible for 3 % of the total burden of disease [2]. Insufficient activity results in annual healthcare expenditures of approximately AUS$850 million, and AUS$15.6 billion in productivity loss [3]. National and international guidelines [4] recommend adults engage in 150–300 min of moderate-intensity (or 75–150 min of vigorous-intensity) aerobic physical activity weekly, and resistance training (RT) on at least two days/week. The prevalence of meeting both aerobic and resistance activity guidelines globally and in Australia is 17 % and 15 % for adults, respectively [5], with fewer Australian adults achieving RT (19–40 %) [[6], [7], [8], [9]] than the aerobic physical activity guidelines (45 %) [8]. Despite the consequences of inactivity and the many health-related benefits [[10], [11], [12], [13], [14], [15], [16]] of meeting both physical activity guidelines [4], few at-scale physical activity interventions have been conducted to improve participation rates [17]. To enhance population physical activity behaviours and health-related outcomes, effective interventions that are ‘scalable’ are needed [18].

Within public health, ‘scale-up’ refers to the “*… deliberate efforts to increase the impact of successfully tested health interventions so as to benefit more people and to foster policy and program development on a lasting basis*” [19]. Some aerobic-based physical activity interventions targeting adults have been scaled-up from efficacy to effectiveness to dissemination, becoming embedded in systems outside of the research setting (e.g., the 10,000 Steps program [[20], [21], [22]]). By comparison, few RT interventions targeting adults have progressed from efficacy to effectiveness [23,24], and to our knowledge, no interventions have been disseminated and implemented on a larger scale. While examples of scaled-up RT interventions exist in school settings (e.g., ‘Resistance Training for Teens’ [25]), the lack of scale-up trials targeting adults is concerning, given the higher proportion of not meeting the RT guidelines [[6], [7], [8]]. It may be that interventions promoting aerobic exercise are easier and cheaper to scale-up compared with those involving RT, as most RT interventions are supervised, include specialised equipment (e.g., weight machines, free weights, elastic resistance bands), are delivered within exercise facilities, and require a different sets of skills (e.g., correct lifting techniques versus going for a walk) [26,27]. Knowledge of the independent health benefits of RT is also more recent than for aerobic activities, providing another potential explanation for this research/practice gap. Regardless, the presence of explicit recommendations to participate in RT warrants a focus on this important, yet often overlooked health behaviour [28].

*ecofit* is a community-based, multi-component intervention that promotes resistance and aerobic physical activity using smartphone technology, the outdoor built environment and social support. The *ecofit* intervention has been evaluated in an efficacy trial targeting adults at risk of/diagnosed with type 2 diabetes, and in an effectiveness trial targeting community-dwelling adults failing to satisfy physical activity recommendations. The efficacy trial showed significant improvements in both primary outcomes (i.e., aerobic fitness and lower body muscular fitness) at the primary time-point, while the effectiveness trial showed significant improvements in upper and lower body muscular fitness at follow-up only [29,30]. For a more detailed account of the efficacy and effectiveness trials, see the published protocols [31,32]. This research protocol will outline the steps guiding the translation pathway of *ecofit* to larger scale implementation [33,34]. Fig. 1 provides a summary of the translation pathway for the ecofit intervention. This will be done by testing a ‘Low’ versus a ‘Moderate’ implementation support model on the *ecofit* intervention in two large regional municipalities in New South Wales, Australia, on the reach (primary outcome), uptake, dose received, impact and fidelity. The planning and design have been guided by the Medical Research Council recommendations for developing and evaluating complex interventions [35] and the Consolidated Framework for Implementation Research (CFIR) [36].

**Fig. 1 fig1:**
[figure not shown]
Research translational continuum of the ecofit intervention.

## Materials and methods

2

### Experimental design

2.1

We will evaluate the implementation of *ecofit* using a hybrid type III implementation-effectiveness trial [37] involving 16 outdoor gym locations randomized to either the (i) ‘Low’ or (ii) ‘Moderate’ implementation support model. Assessments will be conducted at baseline, 3-months (primary and secondary outcomes) and 6-months (secondary outcomes only) and will commence in mid-2024. This implementation-effectiveness trial will be conducted across all outdoor gym locations (N = 16) in the Newcastle City (population n = 173,251) and Lake Macquarie (population n = 202,680) local government municipalities, New South Wales (NSW), Australia. The Standards for Reporting Implementation Studies (StaRI) initiative will be used in the reporting of this study [38]. Our study has received ethical approval from the University of Newcastle Ethics committee (H-2018-0060). The trial has been registered with the Australian and New Zealand Clinical Trial Registry (ANZCTR) (ACTRN12624000261516).

### Recruitment, randomization and blinding

2.2

We have developed a promotional campaign to promote outdoor gym use across both local government municipalities; this will serve as the primary recruitment strategy for the study. The campaign will employ strategies, used in the *ecofit* effectiveness trial [31] and other, similar studies [39], including print and broadcast media, letter drops to all households within the same or adjacent suburbs of each outdoor gym, school/work newsletters, and social media, to promote the *ecofit* app and outdoor gym use. The promotional information will also emphasise the benefits of RT.

Randomization of the park location has already been conducted. Each outdoor gym was pair-matched based on the socioeconomic status of the area surrounding the facilities (high versus low). This classification was estimated using an established socioeconomic status consensus-based index (i.e., the SEIFA index of relative socio-economic advantage and disadvantage) [40]. Parks within each pair were randomized to one of the two conditions (i.e*.,* ‘Low’ or ‘Moderate’ implementation support). The randomization procedure was conducted by a researcher not part of the core research team. The randomization outcome for each location can be found in supplementary material 1. Data collection will be blinded to group allocation.

### Outdoor gym quality audit tool

2.3

As part of this study, an audit was conducted to determine the ‘quality’ of the outdoor gym facilities by a single researcher. Our audit tool was developed for this study, as there were no existing validated instruments for assessing the quality of outdoor gyms. Items include: (i) general cleanliness of equipment (ii) presence of substantial rust on gym equipment, (iii) broken/damaged equipment (percentage of available equipment), (iv) safety issues surrounding equipment, (v) instructional signage or pre-existing QR codes to online instructions (i.e., not QR codes created for this program), (vi) accessibility (i.e., parking within 100 m of facilities), (vii) accessibility (i.e., quality walking paths leading to equipment, (vii) presence of security cameras, and (ix) lighting around the outdoor gym. The items are assessed via ‘yes’ (definitely present), ‘somewhat’ (partly present) and ‘no/none’ (not present). The majority of outdoor gyms were judged as clean with good access and did not have substantial rust or safety hazards related to the outdoor gym area (e.g., broken equipment, sharp edges, fallen branches). Most had existing support on how to use the equipment, lighting was poor in most locations and there were no security cameras present. The audit instrument and results are included in supplementary material 2.

### Intervention components, delivery, and implementation strategies

2.4

This study will assess the implementation-effectiveness of two different implementation support models promoting the ecofit intervention, which are outlined in Fig. 2 (i) Low support (i.e., *ecofit* app): versus (ii) Moderate support (i.e., *ecofit* app, face-to-face workout sessions and QR codes). These implementation support strategies were guided by the findings from our previous studies [30,31,41,42]. See Table 1 for an overview of the two main previous studies.

**Fig. 2 fig2:**
[figure not shown]
Outline of the Low and Moderate implementation support models promoting the ecofit intervention.

**Table 1 tbl1:** Overview of the efficacy and effectiveness trials and key changes.

Efficacy trial design (N = 84) [30,32]	Key changes made for the effectiveness trial	Effectiveness trial design (N = 245) [29,31]	Key changes made for the implementation-effectiveness trial
*Target population:* Adults at risk of, or diagnosed with, type 2 diabetes. *Design:* Two-arm RCT evaluating a 20-week community-based physical activity intervention integrating outdoor built environment (e.g., some outdoor gym equipment, park benches, trees, railings), smartphone technology (i.e., app), and social support (i.e., face-to-face workout and cognitive mentoring sessions). *Intervention:* The intervention group was provided a smartphone application (app), which included workouts and cognitive challenges. In the first 10-weeks of the intervention, participants also received five face-to-face workout/skill-building and psycho-educational sessions. *Primary outcomes:* Aerobic fitness and lower body muscular fitness. *Results:* Significant improvements in aerobic and lower body muscular fitness at the primary time-point (10-wk) and follow-up (20-wk).	• Partnership with Newcastle and Lake Macquarie City Councils. • More inclusive eligibility criteria • Larger sample size. • Removed face-to-face workout and cognitive mentoring sessions. • Developed a more comprehensive smartphone application to substitute the face-to-face component. • Only provided participants with one introductory session and an app manual. • Workouts had more focus on using the outdoor gym equipment to perform exercises. • Primary outcomes targeting muscular fitness only.	*Target population:* Adults not meeting the aerobic and/or the resistance training guidelines. *Design:* Two-arm cluster RCT evaluating a 9-month community-based mHealth physical activity intervention (strong focus on RT), which prescribed workouts using locally available outdoor gym facilities through a smartphone application. To promote social support, participants were able to enrol as groups (of up to 4) and join the *ecofit* Facebook group. *Intervention:* The intervention group was provided with access to a smartphone app, which included standardised workouts tailored to each workout location. In addition, participants had to attend a 90-min introduction session prior to receiving access to the app. *Primary outcomes:* Upper and lower body muscular fitness. *Results:* Significant improvements in upper and lower body muscular fitness at follow-up (9-months), but not at the primary time-point (3-months).	• Shifting focus from individual health-related outcomes to reach and uptake. • Inclusion of more outdoor gym locations (due to recent installations). • Reintroducing face-to-face sessions at the intervention parks. Although, these will not include the psychology-based component. • Intervention parks will also include QR codes to download the app. • Adding a website with introductory videos to the app and a downloadable app manual. • Removing the happiness-item and the 12-min walk/run test from the self-assessment.

### Intervention components

2.5

#### ecofit app

2.5.1

The *ecofit* application has been updated based on feedback from the smartphone app used in the effectiveness trial [29,31] and the need to increase the scalability of its functions from a design perspective. The new *ecofit* platform can be accessed both via a smartphone app downloadable for apple and android devices, as well as via website browsers. The functionality has been improved and expanded upon compared with the previous app [31], and now includes a more scalable approach to tailoring workouts.

The new platform includes (i) videos with real people demonstrating the exercises in an outdoor gym or home-based setting, (ii) written instructions of each exercise alongside the videos, (iii) four different difficulty levels (i.e., level 1 to 4), (iv) ability to choose predetermined or ‘create your own’ workouts, (v) self-monitoring functions (i.e., goal setting and self-assessment tool), (vi) an exercise library, and (vii) resources based on behaviour change techniques [43]. Instead of a face-to-face introductory session, as was used in the effectiveness trial [31], the new *ecofit* platform includes a built-in function that guides users through the app upon registration. Alongside this, users will also have access to an introductory video explaining the purpose of *ecofit* and an onboarding video, which provides an overview of how to use the *ecofit* app. The app will be available to download free of charge, with no exclusion criteria. Informed consent will be collected via the app upon registration. See Fig. 3 for a screenshot of the *ecofit* app homepage and ‘progress’ section.

**Fig. 3 fig3:**
[figure not shown]
Screenshots of the home page and progress page from the ecofit app.

#### ecofit workouts

2.5.2

The workouts on the *ecofit* platform have been expanded upon to suit a broader range of fitness levels. Adaptations include adding more exercises to the overall library, as well as creating another (lower) level of difficulty which targets individuals with low fitness and/or who may have compromised mobility. The difficulty levels for all exercises range from ‘1’ (easiest) to ‘4’ (most difficult) and were determined by an Accredited Exercise Physiologist. The number of sets for each exercise within the workouts range from 1 to 2 (level 1) to 2–3 (levels 2–4) and the number of recommended repetitions is 10 for each set. Upon program commencement, participants will be instructed to initially complete one set of each exercise. When they are able to complete the full set comfortably, they will be encouraged to complete an additional set. When participants can comfortably complete the maximum recommended number of sets per level, they will be instructed to move to the next level.

To support scalability, the new *ecofit* platform uses a multi-component approach to creating workouts. These improvements were based on the results from the process evaluation of the effectiveness trial [44], and meetings between researchers and the app design team. App users can choose a ‘generic workout’ (i.e., includes exercises with minimal equipment that can be performed in a home or park-based setting). For park-based settings, the generic workout assumes that there is a wall, bench and railing available, whereas for the home-based setting, it assumes that there is a bench/chair, wall, and light weights (e.g., food cans, water bottles) available. App users can also choose a workout based on specific locations created by the research team (i.e., the research team has mapped out a workout based on the availability of equipment/facilities available at each outdoor gym included in the study) and/or create their own workout by entering the type of equipment available (i.e., the app will generate a workout based on availability of equipment). App users will have the option to choose a workout that targets a specific area of the body (e.g., full body, upper body with/without core, lower body with/without core or core only). See Fig. 4 for a screenshot on an example ecofit workout and instructions to perform a specific exercise.

**Fig. 4 fig4:**
[figure not shown]
Screenshot of an ecofit workout and instructions of how to perform a specific exercise.

#### Outdoor gyms

2.5.3

All outdoor gym locations (regardless of randomization outcome) will be included on the *ecofit* platform. The characteristics (i.e., type, pieces of equipment, socio-economic status of surrounding suburb) of the outdoor gyms are described in Supplementary material 1. The number of pieces of equipment range from three to 19, and the outdoor gym locations are classified as either ‘trail’, ‘pod’ or ‘trail/pod’, as per an earlier published definition [41]. ‘Trail-based’ outdoor gyms consist of ≥2 exercise stations placed sequentially along an existing walking path, where each station includes ≤3 unique pieces of exercise equipment, or equipment intended for performing ≤3 distinct exercises. ‘Pod-based’ outdoor gyms comprise of one station with ≥4 unique pieces of exercise equipment, or equipment intended for performing ≥4 distinct exercises, clustered to one location. ‘Trail/pod-based’ outdoor gyms utilise a combination of trail- and pod-based (at least one pod), which enable users to engage with the exercise equipment either as part of their transit along the trail or solely within the pod station.

### Implementation strategies

2.6

#### Face-to-face training sessions

2.6.1

Three, 1-h face-to-face, on-site, group-based exercise sessions, led by a trained fitness professional, will be implemented as part of the Moderate implementation support model. The sessions will be conducted within the first month of the intervention, on set times and days (i.e., weekdays and weekends), and individuals can register to attend the sessions free of charge. Each session will encompass a complete standardised resistance and aerobic-based workout, which has been tailored to the outdoor gym location (i.e., workouts will vary pending availability of equipment). Workouts will follow the same structure as in the *ecofit* app (i.e., 3 x upper body, 3 x lower body and 2 x core exercises, and each exercise will be completed as 2 sets of 10 repetitions) [45]. The aerobic component will vary depending on outdoor gym type (i.e., trail, pod, or trail/pod). For outdoor gym pods, the aerobic activity may include short bursts of aerobic activities between each resistance activity (e.g., star jumps, 100-m walk/run out of/back to the pod, marching/running on the spot) or a longer walk/run after completing the resistance-based exercises. The trail locations will provide the opportunity for aerobic activity when moving between equipment. In addition to the workout, the group-based sessions provide an opportunity to ask questions about the *ecofit* app and receive feedback on their exercise technique. To advertise the face-to-face training sessions, posters will be placed on or near the outdoor gym equipment where the workout sessions will be held, along with schools, shopping centres and community notice boards in suburbs surrounding the outdoor gym locations. Exercise sessions will also be advertised via email to those app users who indicate living within the same postcode of the outdoor gyms allocated to Moderate implementation support model, during the app registration.

#### Quick-response (QR) codes

2.6.2

QR codes will be placed next to or near the outdoor gyms included in the locations receiving Moderate implementation support. Scanning the QR code will automatically redirect park visitors to the *ecofit* website and provide information about how to download the app. In recent years, QR codes are becoming increasingly popular to use in various research fields and non-research settings [46]. Websites that include program information and resources have been used in other larger scale physical activity interventions [22].

### Outcomes/measures and data collection

2.7

Based on an evaluation roadmap for scaling-up physical activity and behavioural nutrition interventions [47], a primary outcome (i.e., reach), and several secondary implementation outcomes (i.e., uptake, dose received, impact, fidelity), secondary intervention outcomes (i.e., app usage, acceptability, feasibility and dose satisfaction) and implementation determinants (acceptability, feasibility and satisfaction of face to face sessions and overall cost effectiveness) will be assessed. The primary implementation outcome of ‘reach’ will be measured at baseline and 3-months (primary timepoint). The secondary implementation and intervention outcomes will be measured at baseline, 3-months (primary timepoint) and 6-months (follow-up). Secondary implementation determinants will be assessed following the face-to-face sessions (acceptability, feasibility and satisfaction of face-to-face sessions) and at the conclusion (overall cost-effectiveness) of the study.

#### Primary implementation outcome/measures

2.7.1

##### Reach

2.7.1.1

The primary outcome ‘reach’ is defined as the difference in the absolute number (3-month minus baseline assessments) of outdoor gym users (i.e., people using the outdoor gyms for RT activities) between the two implementation models. This will be measured using a ‘modified version’ of the *System for Observing Play and Recreation in Communities* (SOPARC Resistance Training (hereafter referred to as SOPARC-RT)) [41].

SOPARC-RT has been specifically adapted to capture additional data (not included in the original SOPARC protocol [48]) by coding the interaction with the outdoor gym equipment (i.e., ‘using equipment for RT,’ ‘completing RT without equipment,’ ‘stretching using equipment’ and ‘using equipment for aerobic exercise’) [41]. Each park will have one predetermined target area (i.e., either a pod or one station along a trail) which has been identified for observations during the outdoor gym audit. If the outdoor gym location is classified as a pod/trail, the pod will be selected for observation. At all target areas, one trained research assistant will conduct the observations from a position where the outdoor gym equipment is clearly visible. SOPARC-RT will employ similar recording procedures for ‘jogging tracks’ as per the original SOPARC protocol [48] for all parks regardless of outdoor gym type, and each observation period (shift) will result in 2 h-long observations, as opposed to systematic scans as used in SOPARC. The research assistant observing the target area will code each individual by gender (i.e., woman, man, unsure), and perceived age category (i.e., adult [18–59 years], or senior [60 years or older]). The SOPARC-RT observation tool is attached in supplementary material 3.

The observation schedule will cover two days per park (i.e., one weekday and one weekend day). Each day will be divided into three observation shifts: morning (0600–0800 on weekdays, 0630–0830 on weekends), midday (1200–1400), and evening (1600–1800) [41,48]. Cancelled shifts due to inclement weather (e.g., actual or threat of heavy rain and/or thunderstorm) will be replaced on the following day or on the same day of the subsequent week if weather remains inclement [41,48]. Baseline and follow-up (3-months) observations will be conducted by a team of research assistants over a four-week period at baseline, and 3-months. Pair-matched parks will be observed on the same days. Conducting observations on different days and times over a set period of time is a typical approach for outdoor park observational studies monitoring physical activity [49]. Each park will be assessed over two days with three observation periods per day, totalling six observation periods at baseline and six observation periods at follow-up (3-months). The total number of people observed across these six observation periods will be summed separately for the baseline and follow-up assessments.

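### The weather rule's first choice, the following day, turns a cancelled Friday shift into a weekend observation and a cancelled Sunday shift into a weekday one, against the fixed one-weekday, one-weekend-day schedule

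*Protocol article*

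**What the plan says.** All of this stands in the Reach section (2.7.1.1) of the protocol article, apart from the model terms and planning figure.

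- Schedule: "The observation schedule will cover two days per park (i.e., one weekday and one weekend day").
- Shifts: "morning (0600–0800 on weekdays, 0630–0830 on weekends), midday (1200–1400), and evening (1600–1800"). Only the morning hours depend on the type of day.
- Weather: a shift called off because bad weather has arrived or threatens "will be replaced on the following day or on the same day of the subsequent week if weather remains inclement".
- Pairs: "Pair-matched parks will be observed on the same days". This sentence carries no exception and does not mention replacement shifts.
- Volume: "totalling six observation periods at baseline and six observation periods at follow-up (3-months").
- Count: "The total number of people observed across these six observation periods will be summed separately for the baseline and follow-up assessments".
- Primary outcome: "the difference in the absolute number (3-month minus baseline assessments) of outdoor gym users", compared between the two support models.

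Statistical analysis (2.9) lists group, baseline value and SEIFA stratum as model terms. It lists no term for day type. Its sample size paragraph plans on about 3 users per day per park.

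**The concern.** The schedule balances each park's count at three weekday and three weekend shifts per wave, and sets separate morning hours by day type. The investigators therefore treat day type as relevant. The replacement rule does not carry that condition over. As worded, its first option is the next calendar day, and the option that always keeps the day type comes second, only if the weather stays bad.

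A park that follows the rule can end a wave with a 4 + 2 or 2 + 4 mix. Because the six counts are added without weights and compared with the same park's other wave, part of the recorded change could then come from the calendar. The listed model terms would not absorb it. The text also does not say whether a Friday morning shift moved to Saturday keeps the weekday hours or takes the weekend hours, which start half an hour later; the same question arises for Sunday moved to Monday.

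**Working it through.** **The plan's own figure.** 2 days × 3 shifts = 6 observation periods per park per wave. This agrees with the article.

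**The rule applied to each day of the week.**

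| Cancelled on | Following day | Day type kept? | Same day, next week |
|---|---|---|---|
| Mon, Tue, Wed, Thu | Tue, Wed, Thu, Fri | yes | kept |
| Fri | Sat | **no** (weekday to weekend) | kept |
| Sat | Sun | yes | kept |
| Sun | Mon | **no** (weekend to weekday) | kept |

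The first choice changes the day type on 2 of 7 days. The fallback changes it on 0 of 7. This needs no assumption.

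**How often (assumptions, not in the article).** Suppose scheduled days are spread evenly over the five weekdays and the two weekend days. Then 1/5 of weekday and 1/2 of weekend cancellations replaced next day change type; with equal numbers of each, (1/5 + 1/2)/2 = 35%. If each observation day has probability c of a cancellation that is replaced next day, the chance that a park loses its planned mix in one wave is 1 − (1 − 0.2c)(1 − 0.5c). There are 16 parks × 2 waves = 32 park-waves.

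| c | Chance per park-wave | Expected, of 32 |
|---|---|---|
| 5% | 0.0348 | 1.1 |
| 10% | 0.069 | 2.2 |
| 20% | 0.136 | 4.35 |
| 30% | 0.201 | 6.4 |

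**How much (assumption).** Let a weekday shift draw 1 unit of use and a weekend shift k units. The planned total is 3 + 3k. One crossed shift changes it by (k − 1)/(3 + 3k), and a whole crossed day by three times that.

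- k = 1: no change.
- k = 1.5: 0.5/7.5 = 6.7% for one shift, 20% for three.
- k = 2: 1/9 = 11.1% for one shift, 33% for three.

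**Against ordinary count variation.** The planning figure of about 3 users per day over 2 days gives about 6 per park per wave. One crossed shift is then 6 × 6.7% = 0.4 to 6 × 11.1% = 0.7 of a person. A whole crossed day is 1.2 to 2.0 persons. If the count were Poisson, its standard deviation would be √6 = 2.4, or 41% of 6.

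**The case against.** The sentences can be read together. The one-weekday, one-weekend-day schedule and the same-days rule stand in the same paragraph as the weather rule, and a sensible field team might let them limit the choice of replacement day. The article cites earlier observation protocols for the rule, and a field manual that is not shown may settle the detail. That lowers the likely harm, but the conflict remains: the article states an order of preference, and that order puts the day-type-changing option first.

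A reader might infer that the rule also breaks the same-day pairing. The text does not support this. It is silent on the partner park's shift, while the same-days sentence has no exception and could be read to cover replacements. Nor does the article say that pairing was meant to control for weather or local events: the parks were matched on SEIFA, and the listed model has no pair term. A split pair is only a possibility. At an assumed 10% cancellation rate and a within-pair weather correlation ρ of 0.95 to 0.5, 2 × 0.1 × 0.9 × (1 − ρ) gives 0.9% to 9% of pair-days.

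A reader might also infer a biased comparison between arms. Nothing in the article suggests that cancellations differ by arm: weather does not depend on allocation, and data collection is to be blinded. The objection that this is noise rather than shown bias stands.

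Finally, the article does not name the observation days. If neither Friday nor Sunday is used, the effect is nil. Sunday is, however, one of only two possible weekend days.

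**Conclusion.** The conflict is real and follows from the text alone: for 2 of 7 days, the first-choice replacement changes the day type that the schedule fixes, and the morning hours of such a shift are undefined. It feeds into the primary count without weighting or a listed adjustment.

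The consequence is modest. It arises only if Friday or Sunday shifts are scheduled and cancelled. It is mainly extra noise and poorer comparability between baseline and 3 months for the affected parks. A single crossed shift is well inside ordinary variation of a count near 6; a whole crossed day comes closer to it. The 35%, the 1.1 to 6.4 park-waves and the 6.7% to 33% are illustrations. They rest on an assumed spread of days, cancellation rate and weekend-to-weekday use ratio, none of which the article gives, and should not be taken as estimates for this trial. The point merits a clarification because the remedy is cheap and the fallback already exists.

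**What to change.** Reword the rule along these lines: a shift cancelled for weather is replaced by the same shift on the following day if that day is of the same type (weekday or weekend); otherwise, or if the weather remains inclement, it is replaced on the same day of the subsequent week. Every replacement then keeps its day type and so its morning hours.

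Add one clause saying that the same-days rule for pair-matched parks also applies to replacements where the partner's shift has not yet been observed. Completed partner shifts should not be repeated: that would discard valid data and cost observer time in a study that already reports financial limits on observation.

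The cost is one or two sentences and a wait of about a week for some Friday and Sunday replacements. Such a delay late in the four-week observation period could run past its end, which the existing fallback can already cause, so the text should allow a short extension.
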